## II. Hypothesis and Specific Aims

Our hypothesis is that supplementing pregnant women with sufficient vitamin D will decrease the incidence of allergies, asthma and wheezing illnesses in children. The initial basis for this hypothesis is our finding in two separate birth cohorts of the protective effect of vitamin D intake on wheezing illnesses in 3-5 yr old children. Our birth cohort studies are consistent with data from studies that have investigated animal fetal models and human fetal lung tissue that show that (1) vitamin D receptors are present in the fetal lung, (2) vitamin D enhances lung maturation in the last stages of pregnancy, (3) vitamin D controls growth and development of the fetal lung, and (4) profile of human cord blood cell response to antigens is affected by vitamin D. Finally, there is a large amount of literature that shows that there is a high prevalence of vitamin D deficiency among women of child-bearing age and in pregnant women, such that infants are being born deficient in vitamin D. Furthermore, in both our birth cohorts, vitamin D intake in the first year of life and in childhood did not modify the association of maternal vitamin D intakes with any of the wheeze outcomes. Additionally, there is experimental data that vitamin D affects the development of the neonatal immune system. Taken together, these data strongly suggest that the right time to intervene is during pregnancy. Therefore, we propose a two-arm, randomized, double-blind, placebo-controlled, multi-center clinical trial to determine whether vitamin D supplementation in the pregnant mother will prevent asthma and allergy at age 3. We will utilize asthma/recurrent wheezing as our primary end point and allergy and lower respiratory infection as secondary end points. We will recruit 870 pregnant women during the first trimester of pregnancy and randomize them to one of two treatment arms of a 5-year clinical trial: the addition of 4000 IU daily of vitamin D to usual pregnancy vitamin D supplementation (daily prenatal vitamins with 400 IU vitamin D; total dose in the intervention arm of 4,400 IU/day) in the treatment group compared with placebo plus usual vitamin D supplementation (daily prenatal vitamins with 400 IU vitamin D) in the control group. Because we expect an 8% rate of miscarriages and stillbirths, and about 18% withdrawals or loss to follow-up, we expect that we will have 660 children (330 in each arm) for analysis of the primary outcome at 3 years of age.

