#### IV. Study Overview and Subject Selection

This is a multicenter, randomized, double-blind, controlled clinical trial that compares high-dose vitamin D3 supplementation (4,400 IU/day) vs. usual dose vitamin D3 supplementation (400 IU/day) in pregnancy to prevent asthma in the women's children. The study base will be all pregnant women from each Clinical Center who have a personal history of asthma and/or allergies or a history of asthma and/or allergies in the biologic father of the child (i.e. a "high risk" cohort for asthma and allergies in the child). Eight hundred seventy women (435 in each arm) will be followed through their pregnancy and delivery, and their infants will be followed up to the age of 3 yrs. All infants who are consuming < 1000 ml of formula per day will be offered vitamin D supplementation (400 IU/day) in accordance with the most recent recommendations from the American Academy of Pediatrics. This includes all infants who are breastfed, either partially or exclusively, and all formula-fed infants until they consume at least 1000 ml of formula. The primary outcomes are doctor-diagnosis of asthma and recurrent wheezing at age 3 yrs. Due to dropouts from miscarriages, stillbirths, other pregnancy complications, and loss-to-follow-up, we expect that we will be left with 660 3-yr old children (330 in each arm) for the analyses of the primary outcome (see Specific Aims in Section II above).

Women who come into their Obstetrician's clinics for their first pre-natal visit will be screened on a daily basis by a Study Coordinator and a physician co-investigator will verify eligibility criteria.

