where the parameters are as defined in Specific Aim 1. The  $k$  measured covariates for these analyses will be environmental, maternal, and child factors specific to 25(OH)D levels, such as sun exposure behavior, dietary intake of Vitamin D, and ethnicity. Additionally, any relevant covariates from Table 9 demonstrating main effects that have biologically plausible interactions with Vitamin D supplementation will be tested for effect modification. For both models, it is assumed that  $\varepsilon_i \sim N(0, \sigma^2)$ . The hypothesis that  $\delta_k=0$  will be used to examine whether any of these factors predict 25(OH)D levels, and the results will be used to adjust for any distributional imbalances of these factors across Vitamin D supplementation groups. As with the previous specific aims, we will also tests for effect modification via the hypothesis that  $\eta_k=0$ , or whether any maternal, child, or demographic/environmental covariates modify the relationship between vitamin D intake and circulating 25(OH)D levels in mother's plasma or cord blood. Additionally, we will follow the guidelines outlined in Specific Aim 2 to obtain the most parsimonious model.

The hypothesis that 25(OH)D levels in the child's blood will be higher in the 4400 IU group at birth, age 1 and age 3 will be tested using a repeated measures analysis framework such as generalized estimating equations.

#### P.2.d. Plan for Specific Aim 5

This specific aim investigates whether sufficient vitamin D supplementation in the pregnant mother is associated with reduced incidence of preterm birth (birth <37 weeks gestation) and/or preeclampsia, gestational hypertension, and/or HELLP syndrome compared to a usual care control group in VDAART.

The hypothesis that the incidence of preterm birth/preeclampsia, gestational hypertension and HELLP syndrome (PB/PE) is reduced in the high-dose vitamin D supplementation will be tested using logistic regression, allowing for fixed effect of center. Additional analysis will consider the modification of vitamin D exposure effects by maternal demographic/behavioral factors such as maternal age, BMI and weight gain during pregnancy, and maternal history of asthma/allergy, race, and other factors potentially associated with preterm birth/preeclampsia, gestational hypertension, HELLP or vitamin D exposure.

Letting  $M_i$  be an indicator function for the primary endpoint, PB/PE, for the  $i^{\text{th}}$  subject, the model is:

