### P.3 Multiple comparisons.

All pre-specified hypotheses will be tested individually at the 0.05 level of significance, using a conservative two-sided alternative hypothesis (even when the stated hypothesis is one-sided). More specifically, the primary and secondary hypotheses of Vitamin D supplementation and Asthma/Recurrent Wheeze, Allergy/Eczema/LRI, will not be adjusted for multiple comparisons, since they have been defined a priori and are limited in scope. Additionally, an interim analysis plan has been developed for the primary outcome to adjust for the number of times (3) asthma and/or recurrent wheeze will be analyzed over the study period. Since 25(OH)D status is being examined in 5 separate analyses (maternal plasma at 26-28 weeks, maternal plasma at delivery, cord blood at delivery, infant plasma at years 1 and 3), this analysis will be adjusted for 5 multiple comparisons (i.e., using Bonferroni correction). Finally, any findings with respect to interaction terms (i.e., exploring whether environmental and demographic covariates affect the relationship between Vitamin D supplementation and the outcome of interest) for any of the hypotheses will be adjusted (i.e., using FDR methodology) for the number of models tested, and interaction testing will be limited to those defined in sections D.14.2a-c, in order to limit the potential for spurious findings. Any serendipitous findings coming from exploratory analyses will be clearly reported as such, and test statistic p-values will be adjusted by the number of exploratory hypotheses considered (using FDR or another appropriate procedure for multiple comparisons adjustment).

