#### **Q.5. Power for Specific Aim 5.**

The trial is 84% powered to detect a 50% reduction in PB/PE in pregnant mothers in the vitamin D supplemented (4,400 IU/day) group. We estimate that the incidence of preeclampsia and/or spontaneous preterm labor in the standard dosing group (400 IU/day) will be 10%, resulting in an estimated sample size of 435 subjects per arm at the end of the antenatal period. Our sample size simulations, show that we will have excellent power to detect a 50% reduction in preeclampsia and/or preterm labor in the vitamin D supplemented group which is what we anticipate based on our preliminary data.

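### Aim 5's stated 84% power rests on all 435 randomised women per arm and is about 80% two-sided at that size, about 77% after the plan's own 8% pregnancy loss; P.2.d gives no rule for scoring those losses

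*Supplement*

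**What the plan says.** The Aim 5 plan (the second section numbered P.2.d in the Current Protocol) tests for "reduced incidence of preterm birth (birth <37 weeks gestation) and/or preeclampsia, gestational hypertension, and/or HELLP syndrome compared to a usual care control group". The outcome is a yes/no indicator M_i for each subject, analysed by logistic regression with centre as a fixed effect. The section does not mention miscarriage or stillbirth, does not say whether birth means live birth, and does not name the women in the denominator.

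Section Q.5 gives the power: "The trial is 84% powered to detect a 50% reduction in PB/PE in pregnant mothers" taking the supplement. It puts the rate "in the standard dosing group (400 IU/day) will be 10" per cent, "resulting in an estimated sample size of 435 subjects per arm at the end of the antenatal period".

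Three other places bear on that number:
- Section IV: "Eight hundred seventy women (435 in each arm) will be followed through their pregnancy and delivery". So 435 per arm is the full randomised number.
- Section II: "Because we expect an 8% rate of miscarriages and stillbirths, and about 18% withdrawals or loss to follow-up". Women are randomised at 10 to 18 weeks, so these losses can follow randomisation.
- Section Q.2, for maternal vitamin D levels around delivery, removes the 8%, leaves 400 per arm, and expects no other material loss by then.

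On the test level, P.3 says: "All pre-specified hypotheses will be tested individually at the 0.05 level of significance, using a conservative two-sided alternative hypothesis". P.1 and the Addendum to Analysis Plan both call for intention to treat. The Addendum does not define the Aim 5 outcome.

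**The concern.** Q.2 and Q.5 describe nearly the same moment in the trial with different numbers of women. Q.5 carries the larger number, which makes no allowance for the pregnancies that the plan expects to lose. A reader who takes 84% at face value would overrate what a null result on Aim 5 means.

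The second part concerns the outcome itself. An early miscarriage ends the chance of a preterm delivery. A stillbirth before 37 weeks might or might not count as a birth before 37 weeks. With no rule, an analyst could leave such women out, score them as non-events or score them as events, and could choose after seeing the data. These women are about as numerous as the expected events, so the choice can change the estimated risk ratio and the power.

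**Working it through.** **Inputs.** 10% control rate and a 50% reduction, so 5% treated (Q.5); two-sided 0.05, critical value 1.96 (P.3); 435 per arm (Q.5, Section IV); 8% miscarriage and stillbirth (Section II); 400 per arm at delivery (Q.2).

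**Formula.** For two proportions with p̄ = (p1 + p2)/2,

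power = Φ{ [|p1 − p2| − 1.96·√(2p̄(1 − p̄)/n)] / √[(p1(1 − p1) + p2(1 − p2))/n] }.

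**1. The plan's own figure, n = 435, 10% vs 5%.**
- p̄ = 0.075, and √(2 × 0.075 × 0.925/435) = 0.01786, times 1.96 = 0.03500.
- √[(0.0900 + 0.0475)/435] = 0.01778.
- (0.05 − 0.03500)/0.01778 = 0.843, so power = **80.1%**, not 84%.

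Other two-sided methods at 435 per arm:

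| Method | Power |
|---|---|
| Arcsine | 81.0% |
| Unpooled | 80.3% |
| Log-odds Wald | 78.5% |
| Continuity-corrected | 76.2% |
| Simulated logistic Wald, three centres, 3,000 runs | 80.6% |

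None comes within 2 points of 84%. By the formula above, 84% needs 483 per arm, and 435 is the size for 80%. Values near 84% appear only with a one-sided 0.05 test (for example 84.9% at 435 with continuity correction, or 83.9% at 400 on the log-odds scale), which P.3 rules out.

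**2. Losses removed, n = 400.** 870 × 0.92 = 800.4, or 400 per arm, as in Q.2.
- 1.96 × √(0.13875/400) = 0.03650, and √(0.1375/400) = 0.01854.
- (0.05 − 0.03650)/0.01854 = 0.728, so power = **76.7%** (arcsine 77.7%; simulated 76.3% at 399 per arm).

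**3. All 435 kept.** Assume 8% loss in each arm and 10% vs 5% among continuing pregnancies. If a share f of losses is scored as events, each rate becomes 0.92p + 0.08f.

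| Coding of losses | Rates | Risk ratio | Power |
|---|---|---|---|
| All non-events (f = 0) | 9.2% vs 4.6% | 0.50 | 76% |
| Half events (f = 0.5) | 13.2% vs 8.6% | 0.65 | 59% |
| All events (f = 1) | 17.2% vs 12.6% | 0.73 | 48% |

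**4. Losses against events.** Losses: 0.08 × 870 = 69.6, about 35 per arm. Events under the design effect: 435 × (0.10 + 0.05) = 65, or 400 × 0.15 = 60.

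**5. Bias if losses are non-events.** Take no true effect, a 10% rate among continuing pregnancies, and losses of 10% in one arm and 6% in the other. The rates become 0.90 × 10% = 9.0% and 0.94 × 10% = 9.4%.

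**The case against.** The strongest reply is that this is a gap in wording and not a flaw in the analysis. A reader might infer that keeping 435 per arm makes the trial count a lost pregnancy as a good outcome. The documents do not support that: no text sets M_i to 0 after a miscarriage, and 435 appears as a power input. Where the protocol discusses losses elsewhere, it treats them as dropouts (Section IV) or subtracts them (Q.2), which points to exclusion.

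Nor is it right that these outcomes cannot be scored at all. The 8% includes stillbirths, some of which fit birth before 37 weeks, and hypertensive disease can be recorded before a loss. The documents do not split the 8% into early and late losses.

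The direction of bias is also a weak argument. Even a 10% vs 6% imbalance in losses shifts the comparison only to 9.0% vs 9.4%, small beside a designed halving. Exclusion and non-event coding give practically the same power (77% and 76%). The 59% and 48% figures need codings that the plan does not state.

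All of this stands. It does not explain the 84%, or why Q.5 has 435 where Q.2 has 400. The missing-data section, Q.6, does not settle the matter: its first approach is written for children lost to follow-up, its second for those who drop out, and neither mentions a lost pregnancy. Fetal death is collected as a serious adverse event (VII.J), but nothing ties it to the Aim 5 outcome. P.1's expectation that miscarriage is completely at random does not help either, since the figures in steps 2 and 3 already assume equal loss in both arms.

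**Conclusion.** The concern holds for the stated size and power and for the missing rule. It does not extend to a claim that the plan scores losses as successes.

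- **Size and power.** About 4 points of the shortfall (84% to 80%) are there even with all 435 women. About 3 more (80% to 77%) come from the losses that the plan itself expects.
- **Missing rule.** About 70 women have no stated place in the outcome or the denominator, against 60 to 65 expected events. Among the codings left open, power runs from about 77% to 48% and the risk ratio from 0.50 to 0.73. The low end is a bound, reached only if every loss is an event.

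These figures assume equal 8% loss in both arms, no other loss before delivery (as Q.2 expects), and a 10% control rate for the whole composite. Q.5 gives that 10% for preeclampsia and/or spontaneous preterm labor, which is narrower than the outcome analysed, so the true control rate could differ. Aim 5 is a secondary aim, and the primary asthma analysis is not affected.

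**What to change.** In Q.5, replace 435 with the expected number of continuing pregnancies, about 400 per arm, and restate power as about 77% at two-sided 0.05.

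In the Aim 5 plan:
- State one denominator.
- State one coding of miscarriage and of stillbirth, including whether a stillbirth before 37 weeks counts as a birth before 37 weeks.
- Report pregnancy losses by arm.
- Add one sensitivity analysis on all randomised women with every loss counted as an event.

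Restricting the main analysis to pregnancies that reach 20 weeks is one possible denominator, not a requirement. That threshold is not in the documents, and any such restriction conditions on what happens after randomisation, which is why the all-randomised analysis should sit beside it.

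The cost is a few lines of text. The data already come from the monthly record review, the labor and delivery form and the serious adverse event reports. The price is a lower stated power, and a sensitivity analysis that at about 48% power can guard against a misleading benefit but cannot confirm one.

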### P.3 Multiple comparisons.

All pre-specified hypotheses will be tested individually at the 0.05 level of significance, using a conservative two-sided alternative hypothesis (even when the stated hypothesis is one-sided). More specifically, the primary and secondary hypotheses of Vitamin D supplementation and Asthma/Recurrent Wheeze, Allergy/Eczema/LRI, will not be adjusted for multiple comparisons, since they have been defined a priori and are limited in scope. Additionally, an interim analysis plan has been developed for the primary outcome to adjust for the number of times (3) asthma and/or recurrent wheeze will be analyzed over the study period. Since 25(OH)D status is being examined in 5 separate analyses (maternal plasma at 26-28 weeks, maternal plasma at delivery, cord blood at delivery, infant plasma at years 1 and 3), this analysis will be adjusted for 5 multiple comparisons (i.e., using Bonferroni correction). Finally, any findings with respect to interaction terms (i.e., exploring whether environmental and demographic covariates affect the relationship between Vitamin D supplementation and the outcome of interest) for any of the hypotheses will be adjusted (i.e., using FDR methodology) for the number of models tested, and interaction testing will be limited to those defined in sections D.14.2a-c, in order to limit the potential for spurious findings. Any serendipitous findings coming from exploratory analyses will be clearly reported as such, and test statistic p-values will be adjusted by the number of exploratory hypotheses considered (using FDR or another appropriate procedure for multiple comparisons adjustment).

## Q. Power and sample size

**Q.1. Power for Specific Aim 1.** The trial is designed to detect a 25% reduction in asthma and recurrent wheeze incidence at 3 years in the vitamin D supplemented (4400 IU) group. Based on the observational results in the Viva Study, we estimate that the incidence of asthma and/or recurrent wheeze in the standard dosing group (400 IU) will be 40-50%. This incidence estimate is based on observations from Project Viva and the URECA Project. **In project Viva, the prevalence of persistent wheeze is 44% and of asthma is 56.2% in children born to families with parental history of asthma (about twice the prevalence in children without family history).** These estimates are similar to those observed in the URECA Project in children who have turned 2 yrs old. The children in that cohort had a family history (mom or dad) of asthma or allergies. **In the URECA cohort, 99 of 194 (51.0%) children who have reached their 2nd birthday, have experienced "wheezing or asthma by age 2."** These observed rates in 2 cohorts give us confidence that we will see similar rates when we recruit the high-risk (for asthma and allergies in the child) pregnancies for this clinical trial. We anticipate an 8% miscarriage rate and 17-18% LTF among remaining subjects over the study period, resulting in an estimated sample size of 660 subjects (330 per arm) at the end of the study period. Each power estimate is based on 10,000 simulations. The simulations incorporate an interim analysis plan using the Lan-Demets spending function described in section VII.M, although the power may be slightly lower than the estimates presented here. For our group sequential design, we plan to use a Lan-Demets spending function with four approximately equally-spaced looks (with respect to the amount of information collected) and O'Brien-Fleming type bounds. The software program LANDEM (<http://www.biostat.wisc.edu/landemets/>) was used to calculate the stopping boundaries, which were  $|z|=4.3329, 2.9631, 2.3590$ , and  $2.0141$  at the first, second, third, and final looks, respectively. As noted in N.2.A.1, Lan-DeMets procedure provides a spending function approach which does not require pre-specification of the frequency or timing of interim looks. Therefore, the thresholds will be adjusted if the recruitment targets vary or if the need for more frequent monitoring arises. The hypothesis tests are conducted with two-sided alternatives (i.e. a two-sided p-value). The power reflects the proportion of replicates where the Wald test statistic from the hypothesis test of  $\beta_1=0$  is less than the stopping boundary specified for the first, second, or third looks, where  $\beta_1$  is the coefficient for Vitamin D supplementation status from the logistic regression model outlined in section N.2.a. The replication is considered a 'success' if the stopping boundary is exceeded at any of the analysis times. In the simulations, the incidence of asthma and/or recurrent wheeze at the first and second interim looks is proportionate to the overall incidence expected at the end of the study period (i.e. at the first look, the incidence is one-third of the specified rate; at the second look, it is two-thirds). We do not expect incidence rates of 40-50% to be achieved until the third year of follow-up; therefore, the simulations reflect the approximate amount of information anticipated at each interim analysis.

Finally, in the simulation studies, we also incorporate study heterogeneity into the model by varying the incidence of asthma and/or recurrent wheeze in the control group (400 IU Vitamin D) across study sites. The incidence varies by an absolute difference of 10% (i.e., for a mean incidence of 50%, incidence rates varied from 45-55% across study sites). Thus, the absolute reduction in incidence observed in the treated group (4400 IU Vitamin D) will also vary according to baseline incidence in the control group [i.e., assuming a 30% reduction in incidence, a site with a 50% incidence rate in the control group will have a 35% incidence rate (a 15% decrease) in the treated group, while a site with a 45% incidence in controls will have a 31.5% incidence rate (a 13.5% decrease) among supplemented subjects].

**Table 4. Power to detect a 20-30% reduction in asthma and recurrent wheeze for 660 patients in a multi-site study\***

| Mean Incidence of Asthma and/or Recurrent Wheeze in 400 IU group | Percent reduction in Asthma and/or Recurrent Wheeze in 4400 IU group |            |            |
|-------------------------------------------------------------------------|-----------------------------------------------------------------------------|------------|------------|
|                                                                         | 30%                                                                  | 25% | 20% |
| 0.50                                                             | 0.974                                                                       | 0.906      | 0.726      |
| 0.45                                                             | 0.950                                                                       | 0.837      | 0.653      |
| 0.40                                                             | 0.901                                                                       | 0.773      | 0.574      |

\*18% LTF and 8% miscarriage rate

We anticipate that there will be excellent power (91%) to detect a 25% reduction in asthma, assuming a 50% incidence of asthma/recurrent wheeze in the 400 IU dosing group. Even if the children in this study have a lower incidence of asthma and recurrent wheeze than previous cohorts (i.e., 40-45%), we will still have good power (77-84%) to detect a 25% reduction in asthma and/or recurrent wheeze. To assess the potential impact of study center heterogeneity and interim analyses on power, power calculations were conducted without adjustment for study-center and with a single analysis time point at the end of the study period (with a two-sided  $\alpha=0.05$ ). The calculations were performed in STPLAN (<http://biostatistics.mdanderson.org>), using an arcsine approximation for the binomially distributed outcome. Overall, the power estimates were consistently similar to the empirical estimates (shown in Table 5), with at most a 2% difference in absolute power. Therefore, we do not anticipate that multiple study sites or incorporating interim analyses will considerably reduce study power.

**Q.2. Power for Specific Aim 2.** We expect that there will be 400 women in each arm for this analysis due to the 8% miscarriage rate. We do not expect there to be significant LTF by delivery. Like the analysis plan for Specific Aim 1, we plan to incorporate interim analyses, using a Lan-Demets spending function with O'Brien-Fleming type bounds. For this specific aim, we plan for three looks, which results in stopping boundaries of  $|z|=3.7103$ , 2.5114, and 1.993, for the first, second, and final analysis, respectively. As above, the thresholds will be adjusted if the recruitment varies from the expected targets. As shown in Table 5 below, we will have excellent power to detect an increase of 20-60% in the proportion of mothers with 25(OH)D levels > 75 nmol/L between the intervention and the control group. The power calculations did not explicitly account for the interim analyses, however, the power should still be >0.999 even after distributing the alpha level across multiple looks.

**Table 5. Power to detect a 20-60% absolute increase in the proportion of mother's with 25(OH)D > 75 nmol/L for 800 patients in a multi-site study\***

| Proportion of mothers with 25(OH)D > 75 nmol/L in 400 IU group | Proportion of mothers with 25(OH)D > 75 nmol/L in 4400 IU group |            |            |
|--------------------------------------------------------------------------|---------------------------------------------------------------------------|------------|------------|
|                                                                          | 90%                                                                | 80% | 70% |
| 0.50                                                              | >0.999                                                                    | >0.999     | >0.999     |
| 0.40                                                              | >0.999                                                                    | >0.999     | >0.999     |
| 0.30                                                              | >0.999                                                                    | >0.999     | >0.999     |

\* 8% miscarriage rate

**Q.3. Power for Specific Aim 3.** The estimated incidence of doctor's diagnosis of allergy (IgE), eczema, and lower respiratory tract infection (LRI) at year 3 in the Viva cohort are 30%, 36%, and 45%, respectively, among the children with a parental history of asthma or allergies. Estimates of eczema and LRI differ from those submitted in the previous grant application, which were based on incidence of these secondary outcomes among all children (including those without a parental history of asthma and allergies). Additionally, information on allergy incidence in Project Viva is now available. We anticipate a 30%-45% reduction in each of these outcomes in the high-dose vitamin D supplementation (4400 IU) group, though a larger range is provided in table 6 below. Each power calculation is based on 10,000 simulations, and is identical to the simulations described above, except that interim analyses are not planned for the secondary outcomes, and the studies are powered to detect an effect at the end of the three year follow-up period, with a two-sided alpha level of 0.05. As with the methods described above, these simulations incorporate an effect for study center heterogeneity in baseline incidence of secondary outcomes (i.e., incidence across sites varies by 10%) and 8/18% losses to miscarriage and follow-up/miscarriage, respectively.

This specific aim has an interim analysis plan that is identical to the procedure outlines for specific aim 1. While the power estimates below do not directly incorporate the interim looks, we feel that the power reduction will be modest. With a 30% reduction in incidence, we anticipate that there will be good power (83.4%) to detect a clinically important difference in risk of eczema. Due to the lower incidence of allergy, a 35% reduction is required to have very good (89.0%) power. Additionally, since LRI is more prevalent at age 3, only a 25% reduction is required to have 85.8% power. Even if the incidence of these outcomes is 5% lower than the estimated rates in Viva, there will still be sufficient power to detect an effect of treatment. Overall, there is strong evidence that we will be adequately powered to detect a risk difference in treatment group (4400 IU Vitamin D) for the secondary outcomes, in addition to our primary outcome of interest, asthma and recurrent wheeze.

**Table 6. Power to detect a 25-35% reduction in secondary outcomes for 870 subjects in a multi-site study, (effectively 660 patients, assuming an 8% miscarriage rate and 18% loss to follow-up)**

| Mean Incidence of secondary outcome in 400 IU group | Percent reduction in secondary outcome in 4400 IU group |            |            |
|------------------------------------------------------------|----------------------------------------------------------------|------------|------------|
|                                                            | 35%                                                     | 30% | 25% |
| 0.50                                                | 0.998                                                          | 0.982      | 0.913      |
| 0.45                                                | 0.992                                                          | 0.958      | 0.858      |
| 0.40                                                | 0.973                                                          | 0.906      | 0.779      |
| 0.35                                                | 0.936                                                          | 0.845      | 0.691      |
| 0.30                                                | 0.890                                                          | 0.736      | 0.608      |
| 0.25                                                | 0.795                                                          | 0.654      | 0.531      |

**Q.4. Power for Specific Aim 4.** The research to date on the impact of vitamin D supplementation on 25(OH)D is presented in Table 1. As noted in the table, only 4 studies have been conducted on pregnant women, all had fewer than 100 subjects, and the maximum daily dose for these studies was 1,600 IU. The only data available on 25(OH)D status in the supplementation ranges we are proposing has been provided by [name] (unpublished data, see section III). In a study of 347 pregnant women (African Americans, Hispanic,

and Caucasians) on either 4000 IU (supplemented) or 400 IU (control) of Vitamin D daily, the maternal plasma 25(OH) D levels were 115 nmol/L in supplemented subjects, and 80 nmol/L in controls after 8 months of supplementation, an overall difference of 35 nmol/L. The estimated standard deviation for 25(OH)D levels in these ranges is 40.

Based on the observed differences/variation in 25(OH)D levels, we used simulation studies to estimate the power to detect a mean difference of 7.5 – 37 nmol/L across the supplemented and control groups in maternal plasma at 26-28 weeks, as well as maternal plasma and cord blood at delivery, using an estimated standard deviation of 40. We anticipate that the difference in 25(OH)D levels in maternal plasma across treatment groups will be less

pronounced at the 26-28 week measurement period (e.g., 12.5 – 25 nmol/L), and we do not expect to observe a significant difference by supplementation status in circulating vitamin D in infants at 1 and 3 years of age, since no post-natal treatment intervention is planned. The simulations were generated in a similar manner to method described for Specific Aim 2, except that linear regression (rather than logistic) was used to model the relationship between circulating vitamin D and vitamin D supplementation status. Study heterogeneity was incorporated into the model by allowing 25(OH)D levels to vary by 25 nmol/L across study sites. Since this phenotype will be measured five times throughout the study period, the power was defined as the proportion of replicates with a Wald test statistic (i.e., testing the null hypothesis that the coefficient for vitamin D supplementation status is 0) 2-sided p-value was less than 0.01 (0.05/5). Additionally, this specific aim will include 2 interim and a final analysis, which will be identical to the procedure outlines for specific aim 2. While the power estimates below do not directly incorporate the interim looks, we feel that the power reduction will be modest. The results are shown in Table 7.

**Table 7. Power to detect a 7.5 – 37 nmol/L difference in 25(OH)D for 870 subjects in a multi-site study, (effectively 660 patients, assuming an 8% miscarriage rate and 18% loss to follow-up).**

| Mean change in 25(OH)D levels in 4400 IU group (nmol/L) | Power |
|---------------------------------------------------------|-------|
| 7.5                                                     | 0.444 |
| 12.5                                                    | 0.925 |
| 25                                                      | 0.999 |
| 37                                                      | 0.999 |

For a mean difference greater than 7.5 nmol/L, we anticipate having excellent power to detect a difference in 25(OH)D status across treatment groups. This difference of at least this magnitude should be observed in both maternal plasma measurements and cord blood, given the preliminary data (a difference of 35 nmol/L in maternal plasma) provided by [name]. To ensure that the results were not affected by incorporating an effect for study center, the simulations were conducted assuming homogenous effects across study sites. The power estimates were within 1.5% of those provided above, and are likely due to variation in estimates via simulation. Therefore, we are confident that we have excellent power to achieve this specific aim.

